### **6.7. Concomitant Therapy**

Any medication or vaccine (including over the counter or prescription medicines, recreational drugs, vitamins, and/or herbal supplements or other specific categories of interest] that the participant is receiving at the time of enrollment or receives during the study must be recorded along with:

- Reason for use
- Dates of administration including start and end dates
- Dosage information including dose and frequency

The Medical Monitor should be contacted if there are any questions regarding concomitant or prior therapy.

Participants must abstain from taking prescription or nonprescription drugs (including vitamins recreational drugs, and dietary or herbal supplements) within 7 days (or 14 days if the drug is a potential enzyme inducer) or 5 half-lives (whichever is longer) before the start of study intervention until completion of the follow-up visit, unless, in the opinion of the investigator and sponsor, the medication will not interfere with the study.

Metformin is a substrate for the OCT1 and OCT2 transporters. Co-administration of metformin with other drug that are inducers or inhibitors of these transporters should be monitored closely.

Following prior and concomitant therapies should be used cautiously and patient should be closely observed: thiazides and other diuretics, corticosteroids, phenothiazines, thyroid products, estrogens, oral contraceptives, phenytoin, nicotinic acid, sympathomimetics, calcium channel blockers, and isoniazid.

Prior and concomitant therapies listed as prohibited in Table 6 are not permitted for the specific time frames listed. (See Appendix 7)

### **Intravenous Contrast**

The European Society of Urogenital Radiology advocates stopping metformin 48 hours before CT for patients with an eGFR of less than 45 mL/min.

Patients with an eGFR above 60 mL/min who receive a larger amount of intravenous contrast (> 100 mL, e.g., CT of the abdomen or pelvis, CT angiography of the aorta or lower extremities) should restart metformin no earlier than 48 hours after the procedure.

## **7. Discontinuation of Study Intervention and Participant Discontinuation/Withdrawal**

### **7.1. Discontinuation of Study Intervention**

In some instances, it may be necessary for a participant to permanently discontinue study intervention. If study intervention is permanently discontinued, every effort should be made to keep the participant in the study for safety follow-up. See the SoA for data to be collected at the time of discontinuation of study intervention and follow-up and for any further evaluations that need to be completed.

At the baseline visit, patients will be given a list of precautions and reasons for temporarily or permanently discontinuing study medication, as well as a form of contact with the investigator.

#### **7.1.1. Permanent Discontinuation**

Study medication must be permanently discontinued in the following circumstances:

- Diabetes onset
- Hypersensitivity to the active substance or to any of the excipients.
- Unrecovered severe renal failure (eGFR <45 ml/min).
- Any acute metabolic acidosis event (such as lactic acidosis, diabetic ketoacidosis).
- Adverse events or intolerances related to the study medication, at the investigator's discretion.
- Diagnosis of B or C hepatitis infection or any other progressive liver disease.
- Diagnosis of chronic heart failure, or cancer.
- Alcohol abuse:
  - For men, heavy drinking is typically defined as consuming 15 drinks or more per week.
  - For women, heavy drinking is typically defined as consuming 8 drinks or more per week.
- Participants starting other maintenance medications that according to study drug label are contraindicated with metformin. (Appendix 7)
- Pregnancy.
- Any new events, comorbidities or medications that according to the investigator could entail additional risks for the participant.

#### **7.1.2. Temporary Discontinuation**

Study medication must be temporary discontinued in the following circumstances:

- Liver laboratory abnormalities: ALT over 5 times the upper limit of normal (ULN) or ALT over 3xULN and bilirubin over 1.5xULN or any verified Grade 4 laboratory abnormality that to the investigators criteria would affect the safety of the participant.

- Acute disorders that involve a risk of impaired kidney function such as dehydration, severe infection, or shock.
- Acute or chronic disease capable of causing tissue hypoxia, such as heart or respiratory failure, recent myocardial infarction, shock, or stroke.
- Hepatic failure, acute alcohol intoxication, alcoholism.
- Study medication should be stopped at the time of surgical intervention with general, spinal, or epidural anesthesia. Treatment can be restarted 48 hours after the intervention surgical procedure or after resumption of oral feeding, provided renal function has been reassessed and proven to be stable.
- Study medication should be stopped prior to or at the time of intravenous iodinated contrast test and should not be restarted until at least 48 hours, provided kidney function has been reassessed.
- Participants unable to swallow study medication tablets during the treatment period.
- Participants starting other temporary medications that according to study drug label are contraindicated with metformin. (Appendix 7)
- Any new events, comorbidities or medications that according to the investigator could entail additional risks for the participant.

### 7.1.3. Rechallenge

Patients with a permanent or temporary discontinuation will be evaluated by the investigator as soon as possible for safety evaluation and to assess the possibility of re-inclusion.

Rechallenge with the study medication after a temporary discontinuation may be considered at the discretion of the investigator, as long as the event has completely resolved, is not related to the study medication, and the patient agrees to continue the intervention.

In the event of transitory impaired renal function, study medication may be restarted after recovery of an estimated GFR > 45 mL/min.

If the cumulative duration of the interruptions is greater than two months, re-inclusion will not be considered, but study visits will continue as scheduled.

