## 7.2. Participant Discontinuation/Withdrawal from the Study

- In accordance with the current revision of the Declaration of Helsinki (Fortaleza, Brazil October 2013) (World Medical Association. Declaration of Helsinki- Ethical principles for medical research involving human subjects. *World Med Assoc.* 2013) a participant may withdraw from the study at any time at his/her own request without prejudice to the medical care provided by his doctor or referral centre in the future; or may be withdrawn at any time at the discretion of the investigator for safety, behavioral, or compliance reasons. This is expected to be uncommon. Specific reasons for withdrawal:
  - Participant withdraws consent.

- The participant is not willing to comply with the procedures required in the protocol.
  - For safety reasons, especially the occurrence of an event that requires permanent discontinuation of the study medication (see above).
  - Intolerance to the study medication.
  - Pregnancy.
  - Subject is incorrectly included in the study based due to a screening failure.
  - At the discretion of the investigator for any other safety, behavioral, or compliance reasons based on good clinical practice guidelines and clinical judgment.
  - Lost to follow-up.
  - Transfer to another hospital does not necessarily imply withdrawal if the patient wishes to continue in the study and comply with the protocol.
  - A participant may be withdrawn from the study if any AE, SAE, or laboratory safety result occurs, regardless of its relationship to the study medication, that in the opinion of the investigator requires withdrawal because further treatment would jeopardize the safety of the participant.
- The reasons for participants not completing the study will be recorded in the case report form.
  - At the time of discontinuing from the study, if possible, an early discontinuation visit should be conducted, as shown in the SoA. See SoA for data to be collected at the time of study discontinuation and follow-up and for any further evaluations that need to be completed.
  - The participant will be permanently discontinued both from the study intervention and from the study at that time.
  - If the participant withdraws consent for disclosure of future information, the sponsor may retain and continue to use any data collected before such a withdrawal of consent.

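### Section 7.1.3 has permanently discontinued participants assessed for return to study drug, which contradicts the must-stop rule in 7.1.1 and its own next sentence; 7.1, 7.1.2 and 7.2 do not resolve it

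*Protocol*

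**What the plan says.** Section 7.1.1 is mandatory: "Study medication must be permanently discontinued in the following circumstances". The list that follows includes hypersensitivity, any acute metabolic acidosis event, cancer and pregnancy.

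Section 7.1.3, headed Rechallenge, opens with both classes of discontinuation: "Patients with a permanent or temporary discontinuation will be evaluated by the investigator as soon as possible for safety evaluation and to assess the possibility". What is to be assessed, besides safety, is re-inclusion. The next sentence is narrower: "Rechallenge with the study medication after a temporary discontinuation may be considered at the discretion of the investigator", and only "as long as the event has completely resolved, is not related to the study medication, and the patient agrees to continue the intervention". The section ends by providing that, where interruptions add up to more than two months, "re-inclusion will not be considered, but study visits will continue as scheduled".

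Section 7.1 asks that every effort be made to keep a permanently discontinued participant in the study for safety follow-up. Section 7.2 names an event requiring permanent discontinuation among the specific reasons for withdrawal from the study and says of a withdrawn participant: "The participant will be permanently discontinued both from the study intervention and from the study at that time".

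**The concern.** A rule that says drug must stop for good should not need interpretation, yet a site that reads only the first sentence of 7.1.3 is told to consider a permanently stopped participant for return to drug. Whether such a participant then stays in follow-up depends on whether the site follows 7.1 or 7.2. If the event itself could fall in either the permanent or the temporary list, the word on which the rechallenge rule turns is also uncertain.

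The stake is mainly consistent handling of a safety rule. For the analysis, section 9.3 removes post-discontinuation observations from the per-protocol set, so a stop that is called permanent but later reversed would leave that cut-off unclear. The follow-up question is separate: it decides whether the later scheduled visits take place at all for that participant.

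**Working it through.** No figure in the protocol bears on this point and no arithmetic applies. The check sets the passages side by side.

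1. **What re-inclusion means.** The last sentence of 7.1.3 separates it from visit attendance: participants who are not re-included continue their visits. It therefore cannot mean staying in follow-up and must mean returning to study drug. Section 7.1 supports this reading, because a permanently discontinued participant is meant to remain in the study anyway and needs no re-inclusion for that.

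2. **7.1.3, first sentence, against 7.1.1.** Section 7.1.1 makes the stop mandatory and permanent. The first sentence of 7.1.3 includes the same participants in an assessment for return to drug. The two conflict.

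3. **7.1.3, first sentence, against its second.** The first sentence covers permanent and temporary stops. The second permits rechallenge after a temporary stop only, on three conditions: the event has resolved, it is unrelated to study drug, and the participant agrees. For a permanent stop the first sentence orders an assessment to which the second attaches no possible positive outcome.

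4. **The rest of 7.1.3.** The renal sentence concerns transitory impairment, and 7.1.1 lists only unrecovered severe renal failure, so these two are compatible. The two-month limit concerns interruptions. Neither sentence permits a restart after a permanent stop.

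5. **7.1 against 7.2.** Section 7.1 aims to retain a permanently discontinued participant. Section 7.2 gives the event that caused the permanent stop as a reason for withdrawal, and withdrawal ends both drug and study. With the first sentence of 7.1.3, the same participant could be kept in follow-up, withdrawn, or reviewed for return to drug.

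6. **7.1.1 against 7.1.2.** The lists overlap in three places:

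| Permanent list (7.1.1) | Temporary list (7.1.2) |
|---|---|
| Alcohol abuse | Alcoholism |
| Chronic heart failure | Acute or chronic disease causing tissue hypoxia, with heart failure as an example |
| Closing catch-all for new risks in the investigator's judgement | The same catch-all, word for word |

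   An event of these kinds can be assigned to either class, and the class decides whether the rechallenge sentence applies.

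7. **Analysis sets (9.3).** The primary, intention-to-treat-exposed set keeps all observations after discontinuation. The per-protocol set drops them. Section 6.4 requires start and stop dates, including delays, to be recorded.

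**The case against.** The strongest reply is that 7.1.3 orders an evaluation and does not authorise dosing. Its sentence has two purposes, and it can be read so that everyone receives the safety evaluation while the re-inclusion question arises only where the following sentence allows it. Rechallenge is specified for temporary stops, so by ordinary reading it is not available after permanent ones. Section 7.1.1 is mandatory, section 8 allows no waivers, and 7.2 closes off restart for anyone withdrawn.

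Most of this stands, and it rules out three stronger readings that a reader might infer:

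- *Study drug may be restarted without any condition after, say, hypersensitivity or acidosis.* The documents do not support this. The only general permission to restart is confined to temporary stops and carries three conditions, and a two-month limit also applies to re-inclusion.
- *Every circumstance in 7.1.1 is reopened.* None is expressly reopened. Unrecovered renal failure is permanent by its own wording, and several items already rest on the investigator's judgement.
- *The primary analysis is compromised because the discontinuation date is blurred.* Post-discontinuation observations stay in the primary set whatever that date is, and stop dates are recorded.

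The reply does not remove the inconsistency. The distributive reading has to be supplied by the reader; the sentence itself pairs permanent discontinuation with re-inclusion. The reply also leaves untouched the difference between 7.1 and 7.2 over follow-up and the overlap between the two lists.

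**Conclusion.** The concern holds as an internal inconsistency in a must-stop rule. The opening sentence of 7.1.3 contradicts 7.1.1 and the sentence that follows it. Sections 7.1 and 7.2 point in different directions on whether a permanently discontinued participant stays in the study, and 7.1.1 and 7.1.2 overlap, so the class of an event may be unclear. The protocol does not expressly authorise a restart after a permanent stop.

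The size cannot be put as a number. The protocol gives no rate of permanent discontinuation, and no effect on sample size or error rate was identified. Through the discontinuation date, at most the per-protocol cut-off for an individual would be unclear, and only if a restart took place. The conclusion rests on reading re-inclusion as return to drug, which the last sentence of 7.1.3 supports. It is worth correcting because the wording governs a safety rule and the correction is small.

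**What to change.** Reconcile 7.1, 7.1.1, 7.1.2, 7.1.3 and 7.2 so that they agree on three things:

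- whether re-inclusion can apply after a permanent discontinuation, with the opening sentence of 7.1.3 worded to match 7.1.1 and the rechallenge sentence;
- whether a participant with a permanent discontinuation remains in follow-up or is withdrawn;
- which class each overlapping item in 7.1.1 and 7.1.2 belongs to, or how the class is decided.

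Use one term for restarting study drug and a different one for remaining in follow-up. Which clinical rule is right is for the sponsor to decide. The cost is a clarification of a few sentences, with no change to the sample size or to the planned analysis.

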## 7.2. Participant Discontinuation/Withdrawal from the Study

- In accordance with the current revision of the Declaration of Helsinki (Fortaleza, Brazil October 2013) (World Medical Association. Declaration of Helsinki- Ethical principles for medical research involving human subjects. *World Med Assoc.* 2013) a participant may withdraw from the study at any time at his/her own request without prejudice to the medical care provided by his doctor or referral centre in the future; or may be withdrawn at any time at the discretion of the investigator for safety, behavioral, or compliance reasons. This is expected to be uncommon. Specific reasons for withdrawal:
  - Participant withdraws consent.

- The participant is not willing to comply with the procedures required in the protocol.
  - For safety reasons, especially the occurrence of an event that requires permanent discontinuation of the study medication (see above).
  - Intolerance to the study medication.
  - Pregnancy.
  - Subject is incorrectly included in the study based due to a screening failure.
  - At the discretion of the investigator for any other safety, behavioral, or compliance reasons based on good clinical practice guidelines and clinical judgment.
  - Lost to follow-up.
  - Transfer to another hospital does not necessarily imply withdrawal if the patient wishes to continue in the study and comply with the protocol.
  - A participant may be withdrawn from the study if any AE, SAE, or laboratory safety result occurs, regardless of its relationship to the study medication, that in the opinion of the investigator requires withdrawal because further treatment would jeopardize the safety of the participant.
- The reasons for participants not completing the study will be recorded in the case report form.
  - At the time of discontinuing from the study, if possible, an early discontinuation visit should be conducted, as shown in the SoA. See SoA for data to be collected at the time of study discontinuation and follow-up and for any further evaluations that need to be completed.
  - The participant will be permanently discontinued both from the study intervention and from the study at that time.
  - If the participant withdraws consent for disclosure of future information, the sponsor may retain and continue to use any data collected before such a withdrawal of consent.
  - If a participant withdraws from the study, he/she may request destruction of any samples taken and not tested, and the investigator must document this in the site study records.

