| Laboratory test: C-Reactive Protein, D-Dimer, IGF-1, fasting insulin, cystatin C; NT-proBNP                                                                                                        |                                                 | X                                        |          |                        | X         | X         | X         | X         | X          |            |                  |
| Laboratory tests for epigenetic study, complete immune profile  , blood leucocyte telomere length, oxidative stress levels and DNA damage markers, TAME trial biomarkers  |                                                 | X                                        |          |                        |           | X         |           | X         |            | X          |                  |
| Frailty assessments and geriatric scale                                                                                                                                                            |                                                 | X                                        |          |                        |           | X         |           | X         |            | X          |                  |
| Dispense of study medication                                                                                                                                                                       |                                                 | X                                        | X        | X                      | X         | X         | X         |           |            |            |                  |
| Return of medication and treatment compliance                                                                                                                                         |                                                 |                                          | X        | X                      | X         | X         | X         | X         |            |            |                  |

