| Primary                                                                                                                                                                                                                                                                                                    |                                                                                                                                                                                                                                                                                                                                                                                                                                                                                                                                                                   |
| 
 
To evaluate the anti-aging effect of metformin compared to placebo as assessed by difference in epigenetic age acceleration (EAA) by Phenoage at week 96
 
 
Hypothesis (H1): Metformin is superior to placebo as assessed by changes in the EAA by Phenoage
 | 
 
EAA difference by Phenoage epigenetic clock
 
                                                                                                                                                                                                                                                                                                                                                                                                                                                                     |

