### 9.3. Analysis Sets

For the purposes of analysis, the following analysis sets are defined:

| Participant Analysis Set | Description                                                                                                                                            |
|--------------------------|--------------------------------------------------------------------------------------------------------------------------------------------------------|
| Randomized               | Participants who were assigned to one group of study intervention                                                                                      |
| Evaluable                | Participants who received at least 1 dose of study intervention                                                                                        |
| Safety                   | All randomized participants who are exposed to study intervention. Participants will be analyzed according to the intervention they actually received. |

| Defined Analysis Data Sets                                    | Description                                                                                                                                  |
|---------------------------------------------------------------|----------------------------------------------------------------------------------------------------------------------------------------------|
| Analysis set for primary estimand: Intention-to-treat-exposed | All randomized participants who are exposed to study intervention. For participants who discontinue study intervention and/or receive rescue |

|              |                                                                                                                                                                                       |
|--------------|---------------------------------------------------------------------------------------------------------------------------------------------------------------------------------------|
|              | therapy, all post discontinuation or post rescue observations will be included in the analysis set.                                                                                   |
| Per protocol | All randomized participants. For participants who discontinue study intervention and/or receive rescue therapy, post discontinuation or post rescue observations will not be included |

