| 1 serum 8 ml tube.
(ref.455071)
(La Paz University
Hospital laboratory)                                       | [figure not shown] | X                                               |                                          |          | X        | X         | X         | X         | X         | X          | X          |     |
| Urinalysis
(La Paz University
Hospital laboratory)                                                               | [figure not shown] | X                                               | X                                        | X        | X        | X         | X         | X         | X         | X          | X          | X   |

| Collection tubes                                                                               |                                                                                   | Screening
(up to 30
days before
Day 0) | Intervention Period, Visit number [Week] |          |          |           |           |           |           |            |            | E/D |
|------------------------------------------------------------------------------------------------|-----------------------------------------------------------------------------------|-------------------------------------------------|------------------------------------------|----------|----------|-----------|-----------|-----------|-----------|------------|------------|-----|
|                                                                                                |                                                                                   |                                                 | 1
[0]                                 | 2
[4] | 3
[8] | 4
[24] | 5
[48] | 6
[72] | 7
[96] | 8
[120] | 9
[144] |     |
| 4 EDTA 9 ml tubes
(ref. 455036)
1 serum 8 ml tube
(ref.455071)
(IdiPaz laboratory) | [figure not shown] |                                                 | X                                        |          |          |           | X         |           | X         |            | X          |     |

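### Sections 7.1, 7.1.3 and 7.2 disagree on whether a participant who stops study drug stays in the study, so the post-discontinuation data that the primary estimand includes may not be collected

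*Protocol*

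**What the plan says.** **Estimand.** The primary objective (Section 3) is the "difference in epigenetic age acceleration (EAA) by Phenoage at week 96". In Section 9.3 the set for the primary estimand is everyone randomized and exposed, and for those who stop drug "all post discontinuation or post rescue observations will be included in the analysis set". This is treatment-policy handling. The per-protocol set in the same table leaves those observations out.

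**Leaving the study.** Section 7.2 lists specific reasons for study withdrawal. Drug intolerance is one. Another is: "For safety reasons, especially the occurrence of an event that requires permanent discontinuation of the study medication (see above". The reference back is to the drug-stopping list in 7.1.1. Section 7.2 adds: "The participant will be permanently discontinued both from the study intervention and from the study at that time". The same section makes withdrawal by the investigator permissive and expects it to be uncommon.

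**Staying in the study.** Section 7.1 says that after a permanent drug stop "every effort should be made to keep the participant in the study for safety follow-up", and refers to the Schedule of Activities (SoA) for further evaluations. Section 7.1.3 says that once interruptions add up to more than two months, "re-inclusion will not be considered, but study visits will continue as scheduled".

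**Sampling.** The SoA row that begins "Laboratory tests for epigenetic study, complete immune profile" is marked at weeks 0, 48, 96 and 144. So is the Table 4 row for the research-laboratory tubes ("4 EDTA 9 ml tubes"). In both rows the early-discontinuation (E/D) cell is empty. Other rows do carry an E/D mark, for example viral load and CD4/CD8 count in the SoA and urinalysis in Table 4.

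**The concern.** A treatment-policy estimand can be estimated from data only if people who stop drug go on being measured. Here the same participant, for example one who stops for intolerance at week 30, can be kept for weeks 48, 96 and 144 under 7.1 and 7.1.3, or removed from the study under 7.2. Nothing in the protocol says which section governs. Where 7.1 favours retention, the purpose it names is safety follow-up; it does not mention endpoint sampling.

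The loss would probably not be balanced. The protocol itself expects drug-related intolerance: Section 4.3 justifies the titration by gastrointestinal tolerability, Section 6.5 reduces the dose after grade 2 gastrointestinal events, and Section 5.5 replaces participants who withdraw for adverse events or intolerance in the first 8 weeks. If metformin participants leave for these reasons more often than placebo participants, the analysed week-96 data describe people who tolerated their tablets more than the population named in 9.3. A statistical analysis plan can specify how missing values are handled, but it cannot supply blood that was never drawn.

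**Working it through.** **1. What each reading yields for someone who permanently stops drug**

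| Time of drug stop | Kept (7.1, 7.1.3) | Withdrawn (7.2) |
|---|---|---|
| Before week 48 | Week 48, 96 and 144 samples | No post-baseline PhenoAge value |
| Between weeks 48 and 96 | Week 96 and 144 samples | Week 48 value only |

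In the first row a withdrawn participant contributes nothing to the change-from-baseline model of Section 9.4.2. In the second row the repeated-measures model infers week 96 from participants who stayed in the same arm, which is not treatment policy unless leavers behave like stayers. Participants replaced under Section 5.5 after taking drug remain in the exposed set, with no post-baseline value if they have left.

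**2. The plan's own figure**

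Section 9.2 gives 30 per group, 95% confidence and 80% power for a standardized effect above 0.8. Sidedness is not stated; two-sided 0.05 is assumed.

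- Normal approximation, detectable effect: (1.960 + 0.842) × √(2/30) = 0.72.
- Two-sample t test, detectable effect at 80% power: 0.74.
- Power at 0.8 with 30 per arm (t test): 86.1%.

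The stated figure is therefore conservative rather than exact. The 0.74 is used below as the on-drug effect.

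**3. Size of the possible distortion**

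Inputs, all assumed because the protocol gives no rate: on-drug effect D = 0.74 SD; a share q of the metformin arm stops and keeps no benefit; all who stop are withdrawn without usable data; placebo leavers resemble placebo stayers.

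- Treatment-policy effect = D × (1 − q)
- Effect in those still measured = D
- Ratio = 1 / (1 − q)

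| q | Of 30 | Treatment-policy effect | Analysed | Ratio |
|---|---|---|---|---|
| 5% | 1.5 | 0.74 × 0.95 = 0.70 | 0.74 | 1.05 |
| 10% | 3 | 0.74 × 0.90 = 0.67 | 0.74 | 1.11 |
| 20% | 6 | 0.74 × 0.80 = 0.59 | 0.74 | 1.25 |

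The ratio does not depend on D. If only a fraction f of those who stop are withdrawn and the rest are measured, the analysed effect is D(1 − q)/(1 − qf) and the ratio is 1/(1 − qf). At f = 0.5 the ratio is 1/0.975 = 1.03 for q = 5% and 1/0.90 = 1.11 for q = 20%.

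**4. Precision**

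With equal loss of 15% per arm, 30 × 0.85 = 25.5 remain. The detectable effect is then 0.80 and power at 0.8 is 80.0%. At 20% loss (24 per arm) they are 0.83 and 77.4%.

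**The case against.** The strongest reply is that nothing in Section 7.2 makes a drug stop an automatic exit. Investigator withdrawal is permissive, and the sentence that ends drug and study together follows the bullet on people already leaving the study. Two other sections favour retention, and 7.1 sends the reader to the SoA, which sets no on-drug condition on the epigenetic sample. The protocol plainly accepts off-drug sampling, since treatment lasts 96 weeks and week 144 is off drug for everyone. A participant who stops drug and is kept is therefore already scheduled for the primary sample. All of this stands, and it limits the point to a contradiction. It does not remove it: 7.2 still names drug intolerance and drug-stopping events as reasons to leave, and no text gives 7.1 precedence.

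Three stronger inferences are tempting, and the documents do not support them.

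- *Everyone who stops drug is removed.* The wording is discretionary, and withdrawal is expected to be uncommon.
- *The empty E/D cell is what loses the primary endpoint.* A sample on an arbitrary exit date does not give a week-96 value. The empty cell matters mainly because it leaves those withdrawn before week 48 with nothing after baseline.
- *The trial becomes underpowered.* A 15% loss only brings the detectable effect to the protocol's own 0.8, and Section 5.5 replaces some early leavers. Replacement restores numbers but does not undo selection.

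The 5-25% figure is also fairly called a limiting case. Retained benefit in those who stop, week-48 values from later leavers, or partial retention would each reduce it.

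**Conclusion.** The point holds as an internal contradiction with consequences for the primary estimand. Section 9.3 includes data after drug discontinuation, while Sections 7.1, 7.1.3 and 7.2 leave open whether a participant who stops for intolerance or a safety event will be there to provide them. Depending on which section the site follows, such participants may lack a week-96 PhenoAge value, and those withdrawn before week 48 lack any post-baseline value.

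The direction of the distortion is towards an on-drug comparison. Its size cannot be read from the protocol. The 5-25% overstatement (0.74 SD against 0.70-0.59 SD) is an upper illustration that needs 5-20% of the metformin arm to stop, all of them to be withdrawn and none to keep any benefit. With half of them retained and measured it falls to about 3-11%. The textual finding depends on none of these assumptions.

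**What to change.** - **Sections 7.1, 7.1.3 and 7.2:** reconcile them so that stopping study drug, including for intolerance or a safety event, does not by itself end study participation. Leave the other withdrawal reasons (such as withdrawn consent, pregnancy, incorrect inclusion and loss to follow-up) and the investigator's safety discretion in place. The rules on when drug is stopped need no change for this purpose.
- **Section 7.1:** widen the stated purpose of retention from safety follow-up to all scheduled assessments, naming the week 48, 96 and 144 epigenetic samples.
- **Fallback:** mark the E/D cell for the epigenetic row in the SoA and for the research-laboratory tubes in Table 4, and state that this sample does not replace the week-96 value.

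The cost is a minor amendment and a few extra samples, mostly at visits that already exist.
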